### **2.3 Specific objectives**

With the above mentioned purpose the following specific objectives are declared:

1. To evaluate the immunogenicity resulting from the application of the NASVAC TVC to CHB patients, assessing the effect of intranasal / subcutaneous administration on the induced humoral and cellular immune response and finally on the viral load as a variable dependent on immune response, that will be used as the main variable.
2. To identify possible adverse events (AE) linked to the application of the NASVAC TVC to CHB patients and assess their frequency and intensity in the scenery of intranasal/subcutaneous administration.
3. To collect and assess preliminary data on the therapeutic potential of the NASVAC TVC in CHB patients regarding to:
  - Reduction of the serum HBV DNA levels.
  - HBsAg / HBeAg clearance and anti-HBsAg / HBeAg seroconversion
  - Reduction in the levels of transaminase (ALT) activity
  - Clinical outcome of patients (as defined in the corresponding section)

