Further clinical research is required as in case the concept of therapeutic immunization is probed, a large amount of world population will find in therapeutic vaccination a new finite and affordable treatment to overcome current situation.

*All previously presented facts induced the following **working hypothesis**:*

*The administration of NASVAC to CHB patients may subvert tolerance to the surface and core antigens (Ag) of HBV inducing specific immune responses (antibody seroconversion to anti-HBs and anti-HBe), T cells (Th1, CTL) and antigen presenting cells (APCs). Such immune response will favor the control of virus replication and will normalize the transaminases (ALT and AST) in a similar or superior extent to the currently approved treatment Interferon alpha 2b, associated to a lower number of adverse reactions.*

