### **Design of the trial**

The population sample to be tested will be of 160 CHB patients, with variable serum transaminase levels, without treatment for at least 6 months, selected according to inclusion and exclusion criteria and allocated in two study groups (SG). The first study group, SG1 will include 80 CHB patients (HBeAg (+) and HBeAg (-)) that will be treated with 1 mL NASVAC (100 mcg per antigen, per dose per patient), administered in two cycles of inoculations, the first one by the intranasal route with five intranasal inoculations every 14 days each. During the second cycle patients will receive the same dosis (100 mcg per antigen) by the intranasal route and additionally the same dosis by the SC route,

The SG2 will be treated with Alpha-Interferon at standard dosis (weekly injection by SC route).

The treatment is discontinued for all patients of SG1 after completion of both cycles. The evaluation will continue during one year, but an interim report will be released after 5 and 10 administrations.

During the whole treatment period up to one year from the beginning of treatment, the systematic assessment of patients is launched to determine to what extent the treatment has driven them to generate the capacity to control the HBV load. This information is included in Figure 1.

[figure not shown]

**Figure 1.** General Algorithm of the trial

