### Treatment schedule

The NASVAC TVC will be administered **to SG1** during the first cycle in a final volume of 1.0 mL (100µg of HBsAg and 100µg of HBcAg) by intranasal route with 8 actuations of 125 µL until completing . The second cycle will continue the IN administration in the same dosis and frequency and simultaneously the same treatment will be administered by the SC route. The device to be used (Valois VP7D spray pump) will be actuated with five minutes intervals between actuations in the same nostril.

The pegylated IFN will be administered **to SG2** weekly by subcutaneous route in the established dose (180µg) .

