#### **Evaluation criteria regarding safety**

All AE that appear during the study will be recorded in the Case Report Form of each individual.

All medical incidents that occur in the first hour after each administration of the vaccine, causally related or not with the vaccination will be recorded.

The rest of the observations will be evaluated in the follow up visits every 14 days.

The observation includes medical questionnaire of the patient, inspection of the injection site, axillary's temperature, and registration of all symptoms and signs referred by the patient. Explanation of how to act in case of abandonment or exit in the trial

The patients that abandon the trial will always be evaluated, except if the investigator loses contact with him. The information will be registered in the Case Report Form (CRF), including the cause of exit.

Quality control of the evaluation procedure

The clinical and laboratory evaluations will be preserved, in order to be examined by external quality controllers.

All primary data should be collected and conserved during the study.

The frequency of specific determinations as well as the type of determination per specific date according to the protocol are presented below: (Grey boxes: Determinations will not be performed).

| Test                    | Baseline
(not more than 2 months before starting treatment) | Week 12 | Week 24
EOT-V | Week 36 | Week 48
EOT-I | Week 72 | Week 96 | Reference Values
(M: male, F: female) |
|-------------------------|----------------------------------------------------------------|---------|------------------|---------|------------------|---------|---------|------------------------------------------|
| Hemoglobin              |                                                                |         |                  |         |                  |         |         | M: 12-17 g/dL
F: 11.5-15.5 g/dL       |
| Hematocrit (PCV)        |                                                                |         |                  |         |                  |         |         | 37-54%                                   |
| Leukocytes              |                                                                |         |                  |         |                  |         |         | 4-10 x 10  /L                |

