#### **Adverse events (AE)**

To build a table with the frequency of AE per patient for each presented, as well as their severity, to studying which are the most frequent AE.

To study the relationship with the control variables and the appearance of each adverse reaction through a logistic regression analysis where the importance of each variable is obtained in the response prediction and the ratio of probability and conditional probabilities of response for each category of the qualitative variables and for the desired increments of the quantitative variables are estimated.

To compare both treatment groups considering the frequency of AE. For this purpose the chi-square test will be used. In case of quantitative variables that measure the intensity of a reaction, such as fever, blood pressure, ALT increase, etc. the Student's t test will be used, when possible. Otherwise, non parametric tests will be used. Paired tests will be used for the comparison between products and between periods of treatment.

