### **Interim analysis**

After 5 and 10 administrations and also at 48 weeks, patients will be tested by PCR to quantify HBV DNA in serum as well as for HBsAg and HBeAg seroconversion. A comparative study will be conducted for the same variables for internal comparisons between both groups in order to have a reference to standard treatment with a recognized efficacy.

a) A 20% superior percentage of viral load reduction to undetectable levels in the group treated with NASVAC compared to PegIFN treated group in any of the virological study cuts will be considered as a success criteria for the Interim Analysis.

b) A superior difference in the proportion of patients with ALT normalization or combined ALT normalization and viral load reduction to undetectable levels at a defined time (5, 10 dosis or 48 weeks) between groups will be considered a success criteria for the Interim Analysis.

e) A sustained biochemical (ALT) response during three consecutive determinations after dose number 10 will be considered a success criteria.

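### The safety observation names inspection of the injection site but not of the nose, although every NASVAC dosing uses the intranasal route

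*Protocol*

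**What the plan says.** In section 7 of the protocol, under the safety evaluation criteria, the content of the follow-up observation is given as follows: "The observation includes medical questionnaire of the patient, inspection of the injection site, axillary's temperature, and registration of all symptoms and signs referred by the" … No examination of the nose is named there, in the table of determinations that follows, or in the subject management plan of section 11.

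The NASVAC route is set in two places. Under the design of the trial (section 4), cycle 1 is purely nasal: "the first one by the intranasal route with five intranasal inoculations every 14 days each". Under the treatment schedule (section 6), nasal dosing continues in cycle 2 and "simultaneously the same treatment will be administered by the SC route". Interferon is given weekly by the subcutaneous route alone.

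Three other statements depend on how adverse events are found:
- Specific objective 2 (section 2.3) is to identify adverse events of NASVAC and "assess their frequency and intensity in the scenery of intranasal/subcutaneous administration".
- The working hypothesis at the end of section 2.7 expects NASVAC to be "associated to a lower number of adverse reactions" than interferon.
- The adverse event analysis in section 10 plans this: "To compare both treatment groups considering the frequency of AE. For this purpose the chi-square test will be used".

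**The concern.** The examination that is named does not match the main route of the test product. At a cycle 1 dosing there is no injection site to look at, so an examiner who follows the text as written has no local examination to perform. Redness, swelling, erosion or crusting in the nose would then reach the case report form only if the patient noticed and mentioned it, or if a general examination happened to include the nose.

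The sponsor itself treated local nasal tolerance as worth studying: section 2.6.1 reports a nasal irritability study in rats and nasal histopathology.

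Two things are at stake. Objective 2 asks for frequency and intensity by these routes, and the route used most has no named examination. The between-arm test of adverse event frequency would also pool local signs that an examiner looks for at an injection site with nasal signs that nobody is instructed to look for.

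**Working it through.** **1. Count of NASVAC administrations by route.** The inputs are five nasal doses in cycle 1 (design of the trial), nasal plus simultaneous subcutaneous dosing in cycle 2 (treatment schedule), and ten dosing occasions in all, from the interim analysis section: "After 5 and 10 administrations and also at 48 weeks". The five doses in cycle 2 follow by subtraction, 10 − 5 = 5.

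- Nasal administrations: 5 + 5 = 10
- Subcutaneous administrations: 0 + 5 = 5
- Total: 15

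**2. Check against the protocol's own supply figure.** Section 12 lists 30 vials of NASVAC per patient. Section 6 gives a vial volume of 0.5 mL (the resource table prints the volume unit as mL where section 6 has mcL; I use the section 6 value). Each dose is 1.0 mL per route, which agrees with 8 actuations × 125 µL = 1,000 µL. That is two vials per administration:

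- 10 nasal × 2 + 5 subcutaneous × 2 = 20 + 10 = 30 vials

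The supply figure is reproduced, so the 10 : 5 split is sound.

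**3. Coverage of NASVAC by the named examination.**

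- Nasal share of site administrations: 10/15 = 66.7%
- Dosing occasions that involve the nose: 10 of 10
- Dosing occasions with no injection site: 10 − 5 = 5 of 10, all in cycle 1

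**4. Coverage of interferon.** Section 12 provides 48 units over 48 weeks, one per week. Follow-up observations are every 14 days. If that rhythm is kept for 48 weeks:

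- Visits: 48/2 = 24
- Visits per injection: 24/48 = 50%

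At each visit, one of the two preceding injection sites is at least a week old.

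**5. Surveillance stated for one arm only.**

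| Element | NASVAC | Interferon |
|---|---|---|
| Named inspection of a local site | Subcutaneous site only, cycle 2 | Subcutaneous site, at most about one visit per two injections |
| Named inspection of the nose | None | Not applicable |
| Incidents in the first hour after dosing (section 7) | 10 of 10 dosing occasions | None stated for 48 injections |
| ALT/AST after each administration (section 7, below the table of determinations) | Yes | Not stated |

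The second row lowers detection of local signs on NASVAC. The last two rows raise detection on NASVAC, and the adverse event analysis lists a rise in ALT among the reactions to be compared. The protocol gives no rates with which to net these effects.

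**The case against.** The strongest reply is that the nose may well be examined. The list in the safety section is introduced as what the observation includes, so it is not stated to be complete. The same section requires every adverse event to be recorded and takes in whatever the patient reports. Section 7 also mentions a physical examination, section 11 mentions scheduled clinical examinations, and section 8 has each event described as local or systemic. The adverse event forms (Annexes 3A and 3B) are filled in after each dose and are not shown, so they may hold a nasal item. The protocol also uses injection loosely: section 11 speaks of fortnightly injections, which is the NASVAC interval, although the first five doses are nasal. The words may simply mean the site of administration.

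This stands as a limit. A reader might infer that the nose is never inspected; the protocol does not say so. What can be lost is the sign that the patient does not report. Under the section 8 scale, a sign needing no treatment would count as mild. But a general examination does not ensure that the nose is looked at, and the protocol thought the injection site worth naming.

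A reader might also infer that every interferon site is inspected. Weekly dosing with fortnightly visits rules that out.

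Finally, a reader might conclude that the adverse event comparison is tilted towards NASVAC overall. The first-hour recording and the post-dose ALT/AST work the other way, so the documents do not support a net direction. They do not make the comparison sound either, because they too are differences in detection between the arms. Nor can a false-positive rate be put on the test. The protocol gives no local reaction rate and no rate at which patients report nasal signs, and its 0.1 significance level is stated in the serology section, not for adverse events.

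**Conclusion.** The point holds as a gap in the stated procedure. The safety observation names a local examination that does not cover the route used at all ten NASVAC dosing occasions. That route accounts for 10 of 15 site administrations (67%), and in cycle 1 there is no injection site at all. Unreported nasal signs may be missed, which weakens objective 2 and makes detection of local signs differ between the arms.

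The counts rest on five doses in cycle 2, which the 30-vial supply figure supports. The interferon coverage of at most about half rests on fortnightly visits continuing for 48 weeks. Neither the number of signs that would be missed nor the net direction of bias across all adverse events can be derived from the protocol. This is an inexpensive improvement to a safety procedure, not a demonstrated bias in the result.

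**What to change.** In the safety evaluation criteria of section 7, replace the inspection of the injection site with *inspection of every administration site (nasal cavity and injection site)*, carried out at the existing visits in both arms and recorded on the adverse event form. Report local reactions by site, nasal and injection.

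In the adverse event analysis of section 10, base the between-arm test on events found by the same method and at the same visits in both arms. Describe findings from surveillance that exists in one arm only, such as the first-hour recording and the post-dose ALT/AST, per arm and without a test. This second step is needed because adding the nasal inspection does not remove those other differences.

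The cost is one changed sentence in section 7, a line on the form, a short addition to section 10 and a slightly longer visit. NASVAC will probably show a higher recorded rate of local reactions. No dose, schedule or treatment rule changes.

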## **8. Adverse reactions**

### **Adverse events that can be presented and methods to register them**

General AE described for the NASVAC TVC use are generally mild (**see the Reports of Phase I Clinical Trials**)

The investigators will register the information in the CRF, describing their nature (local or systemic), intensity and the necessary treatment to relieve them.

According to WHO guidelines (WHO technical report series N° 850, 1995), the intensity degrees are:

0: No adverse reaction

1: Mild: it does not require treatment

2: Moderate: it requires treatment, and disappears with treatment.

3: Severe: it puts the patient's life in danger or produces the death. It requires prolonged hospitalization, produces significant or persistent disability or congenital malformations.

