### **Procedure for adverse reactions treatment**

1. In case of severe AE the treatment is stopped and the patient is immediately withdrawn from the trial.
2. In case of death, this should be immediately informed to monitors and to the main investigator of study.
3. The hospital should guarantee all the conditions and medications to handle anaphylactic reactions if they appear.
4. Another type of AE will be treated in a symptomatic form according to the rules indicated at each service.

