### **Notification of adverse events (AE)**

Severe AE will be notified to the main investigator and the monitors immediately or before 72 hours after apparition. If a death occurs it will be notified to the monitors before 24 hours of having happened.

Notification should include:

- General data of the patient (group of treatment, age, sex, code number)
- Date of AE, description.
- Treatment applied
- Evolution

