#### **Duties of rest of the investigators**

1. To participate in the meeting that is made to explain the execution of the investigation where they will know their responsibilities.
2. To help principal investigator to include all the patients who fulfill the inclusion criteria.
3. To write down all the information carefully in the CRF, completing all that settled down in the protocol.
4. To maintain a file with the whole documentation related with the investigation, including all the communications with the sponsor, monitors, and with the main investigator, copies of the signed protocol and all modifications that take place, model of included and not included patients, copies of the CRF models of patients, constancy of reception and delivery of the medications and other documents. This file will be available to the monitors and controllers of the quality that carry out the control visits.
5. To participate in the discussion and analysis of the investigation results.
6. To provide the medical attention of the patients those abandon the trial or refuse to participate.
7. To maintain confidentiality of the data included in the trial.
8. To participate in the quality assurance activities that is requested.
9. To control strictly the patient's compliance to treatment by means of the treatment compliance card or by other means.
10. To detect and report to the CIGB and the Ethics Committee of the Hospital, the serious and very serious adverse events those occur.
11. To participate in the final evaluation of the results and in the elaboration of the final report.

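### The adverse event intensity scale mixes need for treatment with seriousness outcomes, so some events have no grade, some fit two, and graded intensity is poorly defined

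*Protocol*

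**What the plan says.** Section 8 (Adverse events that can be presented and methods to register them) sets out four intensity degrees and attributes them to a WHO report. Degree 0 is no reaction. The next two are "1: Mild: it does not require treatment" and "2: Moderate: it requires treatment, and disappears with treatment". Degree 3, severe, covers danger to life and death and continues: "It requires prolonged hospitalization, produces significant or persistent disability or congenital malformations". The same section has investigators record the nature of the event and the treatment needed.

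Intensity is a declared aim. Specific objective 2 is to identify events linked to the vaccine and to "assess their frequency and intensity in the scenery of intranasal/subcutaneous administration". Section 10 (Adverse events) tabulates event frequency "as well as their severity, to studying which are the most frequent AE".

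The top grade also triggers action. Section 5.5 lists severe reactions as a reason for exit. The procedure in Section 8 says: "In case of severe AE the treatment is stopped and the patient is immediately withdrawn from the trial". The notification rule says: "Severe AE will be notified to the main investigator and the monitors immediately or before 72 hours after apparition". In Section 11.2, however, the other investigators are to report "the serious and very serious adverse events those occur" to the sponsor and the hospital Ethics Committee.

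**The concern.** An intensity scale should give every event one grade, and the grade should reflect how bad the event is. This scale changes axis between grade 2 and grade 3. Its lower part asks whether treatment is needed and, for grade 2, whether it works. Its upper part asks whether a serious outcome occurred. No grade rests on symptom burden, loss of function or a laboratory threshold.

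The investigator assigns the grade on the case report form. An intensity that was never recorded on a usable scale cannot be recovered later in an analysis plan. The stakes are the descriptive result on intensity under objective 2, and the meaning of the label that drives exit, withdrawal and notification.

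**Working it through.** The plan states no figure on this point. The check is whether the grades cover every event once, followed by simple arithmetic on the plan's own ALT limits.

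**Coverage.** Cross three attributes that the scale itself uses: treatment required, resolves with treatment, grade 3 outcome present. The text does not say whether the grade 3 outcomes are alternatives. They are treated here as alternatives, which is the reading more favourable to the plan.

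| Treatment required | Resolves with it | Grade 3 outcome | Grades that fit |
|---|---|---|---|
| No | n/a | No | 1 |
| No | n/a | Yes | 1 and 3 |
| Yes | Yes | No | 2 |
| Yes | Yes | Yes | 2 and 3 |
| Yes | No | No | none |
| Yes | No | Yes | 3 |

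Three of the six combinations receive exactly one grade, two receive two grades and one receives none. The overlaps disappear if the higher grade is taken to prevail, although the protocol does not say so. The empty row cannot be filled by any such convention.

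**Laboratory rises.** Inputs: upper limit of normal (ULN) for ALT 42 U/L (Section 7 table) or 40 IU (Section 10, biochemical status); earlier vaccine flares of 1.5 to 3 x ULN, not clinically apparent, in patients who cleared the virus (Section 2.7); limits of 500 U/L and 15 x ULN (Section 5.4).

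- Earlier flares: 1.5 x 42 = 63 U/L, and 3 x 42 = 126 U/L.
- The 500 U/L limit: 500 / 42 = 11.9 x ULN, or 500 / 40 = 12.5 x ULN.
- The 15 x ULN limit: 15 x 42 = 630 U/L, or 15 x 40 = 600 U/L.

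If no treatment is required and no grade 3 outcome occurs, each of these values is grade 1. Section 5.5 makes the appearance of an exclusion criterion a reason for exit, so the limits can end treatment, but they do not change the grade.

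**Terms.** Sections 5.5 and 8 act on *severe*, which is grade 3. Section 11.2 uses two other classes, *serious* and *very serious*. Neither is defined, and neither is mapped to degrees 0 to 3.

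**The case against.** The strongest reply has four parts.

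First, Annex 4 (instructions for the adverse event form) and Annex 5 (scale of adverse events) are listed in Section 9 but are not in the text at hand. Annex 5 could hold finer grading. That limits the claim to Section 8. But Section 8 states the four degrees itself, so a differing annex would have to be reconciled with it.

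Second, a reader might infer that intensity cannot be compared between the arms at all. The protocol does not support that. The same scale applies to both groups. Section 10 compares event frequency by chi-square, and compares fever, blood pressure and ALT increase as quantitative variables. The weakness is mainly in symptoms that are not measured.

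Third, a reader might infer that the grade follows whatever treatment was given. The text speaks of treatment being required. The scale gives no criterion for that need, the trial is open, and other events are treated by each service's own rules, so some dependence on local habit is plausible. It is not stated.

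Fourth, a reader might infer that large liver flares go unmanaged. They do not. The ALT limits and the liver-worsening criterion act outside the grade, and ALT and AST are tested after each vaccine dose. Nor is the span from 42 to 630 U/L a fair measure of harm. Patients may enter with ALT already above the limit, and a 500 U/L limit stands in the same exclusion criterion.

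All four replies narrow the point. None fills the empty row in the table or maps the terms.

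**Conclusion.** The point holds as a defect of definition. On the text of Section 8, one combination of attributes has no grade, two have more than one, and laboratory rises that need no treatment all fall into grade 1. Graded intensity under objective 2 and in the severity table is therefore poorly defined, chiefly for unmeasured symptoms. How many events would be affected cannot be estimated, because the protocol gives no rate for treated events that persist.

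Two further readings should be avoided. A disabling event without hospitalisation can be graded severe, since grade 3 lists disability. The working hypothesis in Section 2.7 expects fewer adverse reactions than with interferon. That is a claim about number, and the scale does not undermine it.

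The conclusion assumes that Section 8 is the operative scale and that Annex 5 does not replace it. Whether the degrees match the cited WHO report cannot be checked here and is not relied on.

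**What to change.** In Section 8 and the adverse event forms (Annexes 3A, 3B and 5):

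- Grade intensity on one exhaustive axis. For symptoms, use effect on daily function. For laboratory values, use multiples of the reference limit that take account of the baseline value. Otherwise a patient who entered with raised ALT would be graded as having an event on the first day.
- Record seriousness (yes or no) and outcome as separate fields, beside the treatment that is already recorded.
- Reconcile *severe* in Sections 5.5 and 8 with *serious and very serious* in Section 11.2, and align Annex 5 with the result. Which field drives exit, withdrawal or notification is for the sponsor to settle; no clinical rule is proposed here.

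The cost is protocol and form wording, and one or two extra fields per event. No visits or tests are added. The change has to be made before events are recorded, because an analysis plan cannot supply the missing grades afterwards.
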